## 2. OBJECTIVES

### 2.1. Primary objective

The main objective of the research conducted as part of the experimental phase (PrevHPV trial) is to evaluate the effectiveness of three components of the intervention, each component being delivered either alone or associated with one or two others, on the vaccination coverage for adolescents (girls and boys) aged 11-14.

### 2.2. Secondary objectives

1. Evaluate the effect of the different components of the intervention, alone or combined, on (i) the vaccination intention of adolescents, parents and GPs, and (ii) knowledge, attitudes, beliefs and practices on infection and HPV vaccination of adolescents, parents, and GPs (including history of vaccine hesitancy), using the KABP-6C questionnaire.
2. Evaluate the impact of the socio-economic level of parents on the effectiveness of the different components of the intervention, alone or combined, on VC in adolescents aged 11-14 years.
3. Evaluate the efficiency (cost-effectiveness) of the different components of the intervention, alone or combined, among adolescents aged 11-14 years.
4. Evaluate the budgetary impact of the different components of the intervention, alone or combined. Note that this objective will only be carried out if the intervention under evaluation is cost-effective (secondary objective 3).
5. Evaluate the implementation of the different components of the intervention, and identify the levers and barriers to implementation at the individual and collective level to assess the transferability of the intervention to other contexts.

## 3. OUTCOMES

### 3.1. Primary outcome

To the primary objective correspond 1 primary outcome and 5 secondary outcomes (see first 2 lines of the table page 15) depending on the number of doses of vaccine administered (1 or 2 doses) and the time of measurement (2 months, 6 months or 12 months after the end of the intervention).

The primary outcome to assess the effectiveness of the different components of the intervention is the vaccination coverage rate (= prevalence of vaccination, i.e. at least 1 dose received) among adolescents aged 11-14 years, 2 months after the end of the intervention. This prevalence will be calculated overall, then separately for girls and boys.

Prevalence is defined as the number of adolescents aged 11 to 14 years who have received at least 1 dose of HPV vaccine (Cervarix®, Gardasil®, Gardasil9®) / the total number of adolescents aged 11 to 14 years. Prevalence before intervention implementation will be calculated among adolescents using the databases of the National Health Data System (SNDS, i.e. the national reimbursement database) (103), data from vaccination centers and family planning centers. We are aware that health insurance coverage for vaccination in boys starting in January 2021, pharmaceutical dispensation among

boys in the SNDS will most likely be close to 0. In the SNDS bases, we will count 14-year-olds who have received at least 1 dose in the last 4 years, 13-year-olds in the last 3 years, 12-year-olds in the last 2 years, and 11-year-olds in the past year.

The prevalence 2 months after the end of the intervention will be calculated using data from the SNDS, data from vaccination centers and family planning centers, and data from vaccination in middle schools. For the same dose of vaccine, it is therefore not possible for an individual to be present in several different data sources, and it is therefore not possible to count people twice. Indeed, if an adolescent (and their parents) decides to be vaccinated following the intervention, he or she has 4 possibilities of access to vaccination: be vaccinated by his or her attending physician (information available in the SNDS via the dispensation of the vaccine in a community pharmacy), get vaccinated in a vaccination center, get vaccinated in a family planning center, or get vaccinated at school as part of the PrevHPV intervention.

The 11-14 years old age group was chosen to calculate the prevalence of vaccination (despite the proposal to vaccinate 11-19 year olds in middle schools - see facilitation of access) because (i) 11-14 year olds are the target for initial vaccination (15-19 year olds = vaccination of catch-up), (ii) those over 14 are in the minority in middle schools.

As indicated above, the prevalence before and at 2 months will be calculated for the entire population of the age group, then separately for girls and boys.

### **3.2. Secondary outcomes**

The secondary outcomes are of two types: (i) those common to the three components of the intervention, evaluated alone or combined; (ii) those specific to one of the three components.

### 3.2.1. Secondary outcomes corresponding to the objectives common to the 3 components

| Specific objectives                                                                                                                                                             | Result                                                                                                                                                                                                          | Outcome measure                                                                                                                                                                                                                                                                                                                                                                                                                                                                                                                                                                                                                        | Time of measure                                                                                    |
|---------------------------------------------------------------------------------------------------------------------------------------------------------------------------------|-----------------------------------------------------------------------------------------------------------------------------------------------------------------------------------------------------------------|----------------------------------------------------------------------------------------------------------------------------------------------------------------------------------------------------------------------------------------------------------------------------------------------------------------------------------------------------------------------------------------------------------------------------------------------------------------------------------------------------------------------------------------------------------------------------------------------------------------------------------------|----------------------------------------------------------------------------------------------------|
| Evaluate the effectiveness of the intervention on the prevalence of vaccination (at least 1 dose received), 6 and 12 months after the end of the intervention (Primary Obj)     | Variation in the prevalence of vaccination (at least 1 dose) between before the start of the intervention and after the end (6 months and 12 months) among young people aged 11 to 14 years                     | Pre-intervention prevalence: number of young people aged 11 to 14 who have received at least one dose of vaccine (SNDS data, vaccination centers, planning centers) / the total number of young people in this age group.
Prevalence after the intervention: number of young people aged 11 to 14 who had received at least one dose of vaccine before the intervention + after the intervention (SNDS data + vaccination centers + planning centers + number of vaccines administered within middle schools) / the total number of young people in this age group.
Calculated globally and separately for boys and girls | Before the intervention
+ At 6 months and 12 months after the end of the intervention           |
| Evaluate the effectiveness of the intervention on the prevalence of complete vaccination (2 doses received), 2, 6 and 12 months after the end of the intervention (Primary Obj) | Variation in the prevalence of complete vaccination (2 doses received) between before the start of the intervention and after the end (2 months, 6 months and 12 months) among young people aged 11 to 15 years | Prevalence before the intervention: number of young people aged 11 to 14 who received two doses of vaccine (SNDS data, vaccination centers, planning centers) / total number of young people in this age group.
Prevalence after the intervention: number of young people aged 11 to 14 who had received two doses of vaccine before the intervention + after the intervention (SNDS data + vaccination centers + planning centers + number of vaccines administered within middle schools) / the total number of young people in this age group.
Calculated globally and separately for boys and girls                   | Before the intervention
+ At 2 months, 6 months and 12 months after the end of the intervention |
| Evaluate the effect of the intervention on parents' intention to vaccinate their child (Secondary Obj 1)                                                                        | Change in the percentage of parents declaring their intention to vaccinate their child between before the start of the intervention and after the end                                                           | KABP-6C questionnaire (see appendix 2 )                                                                                                                                                                                                                                                                                                                                                                                                                                                                                                                                                                                | Before the intervention
+ 2 months after the end of the intervention                            |
| Evaluate the effect of the intervention on whether parents report HPV vaccination in their child (Secondary Obj 1)                                                              | Change in the percentage of parents reporting having had their child vaccinated against HPV between before the start of                                                                                         | KABP-6C questionnaire (see appendix 2 )                                                                                                                                                                                                                                                                                                                                                                                                                                                                                                                                                                                | Before the intervention
+ 2 months after the end of the intervention                            |

|                                                                                                                                                                                                                                    |                                                                                                                                                            |                                                                     |                                                                                                    |
|------------------------------------------------------------------------------------------------------------------------------------------------------------------------------------------------------------------------------------|------------------------------------------------------------------------------------------------------------------------------------------------------------|---------------------------------------------------------------------|----------------------------------------------------------------------------------------------------|
|                                                                                                                                                                                                                                    | the intervention and after the end                                                                                                                         |                                                                     |                                                                                                    |
| Evaluate the effect of the intervention on the knowledge, attitudes and practices (including history of vaccine hesitancy) of parents with regard to HPV infection and HPV vaccine (Secondary Obj 1)                               | Before-after change in percentages or medians of scores obtained on the Likert scales of the questionnaire addressed to parents                            | KABP-6C questionnaire (see appendix 2 )             | Before the intervention
+ 2 months after the end of the intervention                            |
| Evaluate the effect of the intervention on the intention of Grades Eight and Nine students to be vaccinated (Secondary Obj 1)                                                                                                      | Change in the percentage of students declaring their intention to be vaccinated against HPV between before the start of the intervention and after the end | KABP-6C questionnaire (see appendix 2 )             | Before the intervention
+ 2 months after the end of the intervention                            |
| Evaluate the effect of the intervention on the fact that Grades Eight and Nine students declare anti-HPV vaccination (Secondary Obj 1)                                                                                             | Change in the percentage of students reporting having been vaccinated against HPV between before the start of the intervention and after the end           | KABP-6C questionnaire (see appendix 2 )             | Before the intervention
+ 2 months after the end of the intervention                            |
| Evaluate the effect of the intervention on the knowledge, attitudes and practices (including history of vaccine hesitancy) of young people in Grades Eight and Nine with regard to HPV infection and HPV vaccine (Secondary Obj 1) | Before-after change in percentages or medians of the scores obtained on the Likert scales of the questionnaire addressed to Grades Eight and Nine students | KABP-6C questionnaire (see appendix 2 )             | Before the intervention
+ 2 months after the end of the intervention                            |
| Evaluate the effect of the intervention on the intention of GPs to offer vaccination to their patients (Secondary Obj 1)                                                                                                           | Change in the percentage of GPs declaring that they offer vaccination to their patients between before start of the intervention and after the end         | KABP-6C questionnaire (see appendix 2 )             | Before the intervention
+ 2 months after the end of the intervention                            |
| Evaluate the effect of the intervention on the knowledge, attitudes and practices (including history of vaccine hesitancy) of GPs with regard to HPV infection and the anti-HPV vaccine (Secondary Obj 1)                          | Before-after change in percentages or medians of scores obtained on the Likert scales of the questionnaire addressed to GPs                                | KABP-6C questionnaire (see appendix 2 )             | Before the intervention
+ 2 months after the end of the intervention                            |
| Evaluate the impact of socio-economic status on the prevalence of vaccination (1 dose, 2 doses), 2, 6 and 12 months after the end of the intervention (Secondary Obj 2)                                                            | Vaccination prevalence results (1 or 2 doses, and at each time of measure) calculated according to an ecological deprivation index (FDep)                  | Measure corresponding to each outcome
Economic status: SNDS data | Before the intervention
+ At 2 months, 6 months and 12 months after the end of the intervention |

8 For secondary objective 3 (Evaluate the efficiency of the intervention), the outcome is the incremental cost-effectiveness ratio, expressed as additional cost to  
9 increase the vaccination coverage rate (= vaccination prevalence, i.e. at least 1 dose received) by 10% in adolescents aged 11-14 years, 2 months after the end  
0 of the intervention. The costs considered are the costs of the vaccine, the costs of the intervention and its implementation.

1 For secondary objective 4 (Evaluate the budgetary impact of the intervention), the outcome is the annual cost (financial and in terms of health gains) associated  
2 with the generalization of the national intervention in the short and medium term.

3 For secondary objective 5 (Evaluate the implementation of the intervention + levers and barriers to implementation), the outcomes are the following four criteria:  
4 (i) the dose of the intervention (dose of the intervention delivered and received by the target population), (ii) the fidelity of the intervention (gap between the  
5 planned intervention and the intervention actually implemented), (iii) the achievement of the target (participation of the target population in the different  
6 components of the intervention), and (iv) the adaptation of the different components of the intervention to different specific contexts (disadvantaged middle  
7 schools - REP / REP+, medical deserts, etc.).

### 3.2.2. Secondary outcomes corresponding to objectives specific to a component

| Specific objectives                                                                                                           | Result                                                                               | Outcome measure                                                                                                              | Time of measure                                            |
|-------------------------------------------------------------------------------------------------------------------------------|--------------------------------------------------------------------------------------|------------------------------------------------------------------------------------------------------------------------------|------------------------------------------------------------|
| 'Education, Mobilization, Motivation' component                                                                        |                                                                                      |                                                                                                                              |                                                            |
| Evaluate vaccine hesitancy among health students and middle school staff (teachers / nurses / doctors / administrative staff) | Vaccine hesitancy                                                                    | Vaccine Confidence Scale 5C Scale                                                                                            | Before the training of health students                     |
| Assess health students' knowledge of HPV infection and HPV vaccine                                                            | Percentage of students providing accurate answers to the questionnaire               | Multiple choice quiz on HPV infections and prevention                                                                        | Before the training of health students                     |
| Evaluate health students' satisfaction with the intervention (Secondary Obj. 5)                                               | Student satisfaction                                                                 | Self-administered questionnaire                                                                                              | After the intervention                                     |
| Evaluate the satisfaction of middle school professionals with the intervention (Secondary Obj. 5)                             | Satisfaction of middle school staff                                                  | Self-administered questionnaire                                                                                              | After the intervention                                     |
| Evaluate the use of the e-health tools by the target population (Secondary Obj. 5)                                            | Use of tools in participating groups                                                 | Number of connexions                                                                                                         | Monthly after the start of the intervention                |
| Evaluate user satisfaction with e-health tools (Secondary Obj. 5)                                                             | User satisfaction                                                                    | Self-administered questionnaire                                                                                              | After the intervention                                     |
| 'Training of GPs' component                                                                                            |                                                                                      |                                                                                                                              |                                                            |
| Evaluate the interest of GPs in training in motivational interviewing and the decision aid tool (Secondary Obj. 5)            | Percentage of GPs participating in the training and using the decision aid tool      | Number of healthcare professionals present and declaring use of the tool                                                     | During training sessions and after                         |
| Evaluate the effect of training on GPs' communication skills and decision support                                             | Percentage of GPs declaring themselves competent in communication on the vaccine     | Self-administered questionnaire                                                                                              | At 2 months, 6 months and 12 months after the intervention |
| 'Facilitation of access to vaccination' component                                                                      |                                                                                      |                                                                                                                              |                                                            |
| Evaluate acceptance of vaccination in middle schools (Secondary Obj. 5)                                                       | Percentage of young people aged 11 to 14 who initiated vaccination in middle schools | Number of doses of vaccine administered in middle school / number of young people eligible for vaccination within the school | Vaccination day                                            |
| Evaluate the satisfaction of teenagers with regard to the intervention (Secondary Obj. 5)                                     | Adolescent satisfaction                                                              | Self-administered questionnaire                                                                                              | After the intervention                                     |
| Evaluate the satisfaction of middle school staff with the intervention (Secondary Obj. 5)                                     | Satisfaction of middle school staff                                                  | Self-administered questionnaire                                                                                              | After the intervention                                     |

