A KABP-6C survey, at the individual level, repeated cross-sectionally (pre and post interventions) will make it possible to answer secondary objective 1 of the PrevHPV trial and thus to assess knowledge, attitudes, beliefs and practices. The KABP-6C questionnaire will be administered to volunteers in the following populations:

- Students, girls and boys, enrolled in Grades Eight and Nine in one of the public or private middle schools in the 90 municipalities of groups 1 to 6 before the implementation of the components in middle schools (December 2020) and after (May 2021).
- Parents, fathers and mothers of girls and/or boys enrolled in Grades Six through Nine in one of the public or private middle schools in the 90 municipalities of groups 1 to 6 before the implementation of the middle school components (December 2020) and after (May 2021).
- GPs practicing regular consultations with adolescents in the 60 municipalities of groups 1, 2, 5 and 6 before the implementation of the component (December 2020) and after (April 2021).

Costs and implementation indicators are collected prospectively by the referent of each middle school with the help of the PrevHPV project manager of the geographical sector concerned, as the different components of the intervention are implemented.

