## **6. DISTINCTION BETWEEN USUAL CARE AND RESEARCH**

This research does not modify the usual care of the targeted populations. Regarding interventions with adolescents, we offer tools that may or may not be used because the project is essentially based on what already exists. Indeed, human papillomavirus (HPV) can be addressed through different disciplines and through different themes such as those linked to vaccination or sexuality education provided during cycle 4 (Grades 7 to 9).

Through the intervention offering vaccination within middle schools, the project simply aims to facilitate adolescents' access to vaccination by putting them in direct contact with Mobile Vaccination Teams.

**The only procedures added as part of this research are self-administered questionnaires (KABP-6C + satisfaction questionnaires).**

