The correspondence between inclusion number (which will make it possible to establish the link between T0 and T1, and between children and parents) and the identity of the participants will only be documented in the students' individual correspondence notebook and on the list kept for each class by the middle school's research referent. These lists will be destroyed after the questionnaires are administered to T1 in each class. Investigators will not have access to these lists.

(ii) KABP-6C survey among GPs:

For each of the municipalities in groups 1, 2, 5, and 6 the list of GPs practicing within each of them is established. These GPs are then contacted by telephone to ask them to participate in the KABP-6C survey. Each participant will be assigned an inclusion number which will make it possible to establish the link between the pre- and post-intervention questionnaires (T0 and T1).

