### ***10.1. Description of collected data***

The data collected to meet the objectives of this research are as follows. They were defined with a care for minimization:

- a) The main characteristics (number of middle schools, department, FDep, medical density) of the participating municipalities, as well as the participating middle schools (size of the middle school, REP(+) middle school or not, number of FTE school nurses/doctor, urban sector or rural).
- b) The main characteristics of GPs (age group, gender, seniority and area of practice, mode of practice, sector of practice).
- c) The data completing the SNDS data for the calculation of the vaccination coverage rate (1 dose, 2 doses) at the different times (before intervention, 2, 6 and 12 months after the end of the intervention) i.e., for each participating municipality, injection statistics in family planning and education centers and vaccination centers, as well as the number of vaccines administered in each middle school in groups 1 and 3 during the intervention.
- d) Data on individual characteristics, knowledge, attitudes, beliefs (opinions on the effectiveness, safety or usefulness of the vaccine), practices related to vaccination in general and HPV vaccination, antecedents of hesitancy vaccination, intention to vaccinate among adolescents, their parents, and GPs, and declared vaccination status.
- e) Data on health students' knowledge and vaccine hesitancy.
- f) Data on the satisfaction of the different target populations in relation to the actions implemented (SeSa students, middle school professionals, GPs/training, adolescents and parents/e-health tools made available).
- g) Data on the number of middle schools/municipalities asked to participate in the research and the number who accepted, the number and nature of the actions carried out for each of the 3 components, the participation of the target populations in the various actions carried out, possible adaptation of actions (compared to what was planned) according to the context and/or local constraints.
- h) Cost data: resources associated with each of the 3 components (design + implementation), collected from the project teams in charge of their development (for the tools), middle school referents, project managers and training centers. vaccination (for their implementation).

The data collected in b, d, e, and f are collected individually but anonymously, that is to say without collection of indirectly identifying variables.

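### The objective on GP communication skills is worded as a training effect, but only post-training percentages are scheduled, with no baseline and no named comparison group

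*Protocol*

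**What the plan says.** Section 3.2.2, under the GP training component, gives the objective as "Evaluate the effect of training on GPs' communication skills and decision support". The result is the "Percentage of GPs declaring themselves competent in communication on the vaccine", the instrument is a self-administered questionnaire, and the time of measure is "At 2 months, 6 months and 12 months after the intervention". The row names no comparison group and is not linked to a numbered secondary objective. Section 11.3.2 does not mention this outcome.

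The GP outcomes in Section 3.2.1 are set up differently. They name the KABP-6C questionnaire, are timed before and 2 months after the intervention, and are expressed as changes, for example "Before-after change in percentages or medians of scores obtained on the Likert scales of the questionnaire addressed to GPs".

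That survey also reaches untrained GPs. Section 4.2 gives it to "GPs practicing regular consultations with adolescents in the 60 municipalities of groups 1, 2, 5 and 6 before the implementation of the component (December 2020)"; a second round follows in April 2021. Section 7.4 confirms the coverage: "For each of the municipalities in groups 1, 2, 5, and 6 the list of GPs practicing within each of them is established". Group 6 receives no intervention.

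**The concern.** An effect is a contrast, either with the same GPs before training or with comparable GPs who were not offered it. The row fixes neither. Training is voluntary (Section 5.2 requires agreement to take part) and is non-binding e-learning (Section 8). If only GPs who took the course answer, a high percentage could reflect earlier competence or the motivation of those who volunteered, as well as the training.

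The missing baseline matters most, because it is a decision about data collection. A statistical analysis plan can choose a model or name a contrast later. It cannot supply a pre-training answer that nobody collected, and the GP baseline window is December 2020 (Section 4.3).

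**Working it through.** The Protocol gives no sample size, power or expected value for this outcome, so there is no figure to reproduce. The check sets the relevant places side by side and adds one piece of arithmetic.

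**1. Is the missing baseline just table style?** No. Where a baseline is wanted, the tables say so. The GP rows of Section 3.2.1 are changes with a measurement before the intervention, and Section 3.2.2 itself times the health-student assessments before their training. The GP communication row lists post-intervention times only.

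**2. Which questionnaire could carry the item?** Section 6 limits the added procedures: "The only procedures added as part of this research are self-administered questionnaires (KABP-6C + satisfaction questionnaires".
- The KABP-6C is given twice, at T0 and T1 (Section 7.5). It may supply one post-intervention value but cannot supply values at 2, 6 and 12 months.
- The satisfaction questionnaires cover "SeSa students, middle school professionals, GPs/training, adolescents and parents/e-health tools made available" (Section 10.1). For GPs they concern the training, so they have no evident place for GPs who were not trained.

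No questionnaire covering all three times is therefore assigned to untrained GPs.

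**3. What does a post-only percentage say about change?** Let p be the percentage declaring competence after training and b the unknown percentage before. The change is p - b, with b anywhere from 0 to 100. The change therefore lies between p - 100 and p, an interval always 100 points wide.

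With p = 70 (assumed; the Protocol gives no value):
- b = 0 gives 70 - 0 = +70 points;
- b = 100 gives 70 - 100 = -30 points.

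Cutting the range off at 0 would assume that training cannot lower self-rated competence. The same interval applies if b is the unknown percentage in an untrained group.

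**4. What contrast does the design already offer?** With 15 municipalities per group, groups 1, 2 and 5 give 3 x 15 = 45 municipalities offered training and group 6 gives 15 not offered it, 60 in all, as in Section 4.2. Groups 5 and 6 differ only in GP training. Groups 1 and 2 also receive the education component (group 1 facilitated access as well), and their counterparts without GP training, groups 3 and 4, are not in the GP survey. Group 5 versus group 6 is therefore the clean contrast. Section 7.4 links each GP's T0 and T1 answers by an inclusion number, so baseline adjustment is feasible.

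**5. Do the times fit together?** Section 4.3 ends GP training on 31 March 2021 and places the GP T1 survey in April 2021, directly afterwards. Section 4.2 runs the component to April 2021. Sections 3.2.1 and 3.2.2 both call for a measurement at 2 months. Section 7.8.1 ends the research with the April-May 2021 questionnaires, whereas 6 and 12 months after 31 March 2021 fall at the end of September 2021 and the end of March 2022.

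**The case against.** The strongest reply is that only half of the gap is on the page. The row refers to GPs without restriction, whereas the row before it speaks of GPs who take part in the training. Untrained GPs could therefore be meant to answer. The KABP-6C items are in appendix 2, which is not shown; a competence item may already be there, with a T0 value and group 6 included. Municipalities are randomised, so even a post-only comparison by allocated group would be valid without a baseline. The choice of comparator and model may properly sit in the statistical analysis plan. The wider effect on GPs' intentions, knowledge, attitudes and practices is already a before-after outcome with an untrained group.

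Much of this stands. A reader might infer that untrained GPs are left out, that the item is absent from the KABP-6C, or that no training effect can be estimated in this trial. The documents support none of these as fact. What does not fall away is the row itself: it schedules no pre-training value, names no comparator, and, unlike the GP rows of Section 3.2.1, is not tied to the KABP-6C. Two KABP-6C occasions also cannot provide its 6- and 12-month values.

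**Conclusion.** The point holds as a mismatch between the objective and the measurement as written. The absent baseline is explicit. The absent comparison group is an inference from what the Protocol assigns to whom, since untrained GPs are not expressly ruled out. On that footing the outcome describes self-declared competence after training and leaves the effect undetermined: -30 to +70 points for an assumed 70%.

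The trial's structure can support an estimate once the item is asked of the right GPs at the right times. The consequence is limited. This is a component-specific secondary outcome, and neither the primary vaccination-coverage result nor its analysis depends on it. It is worth correcting because the baseline cannot be recovered after training begins.

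**What to change.** - Include the same competence item in the GP KABP-6C questionnaire at T0 and T1 in groups 1, 2, 5 and 6. If appendix 2 already contains it, tie the Section 3.2.2 row to that item.
- Define the outcome as the T1 difference by allocated group among all surveyed GPs, primarily group 5 versus group 6, adjusted for the T0 answer and with clustering by municipality.
- Do not compare training participants with group 6. Uptake is voluntary, so that comparison would bring the self-selection back.
- State that the contrast estimates the effect of offering training, diluted by GPs who do not take it up. Selective response to the survey remains a limitation.
- Keep the 6- and 12-month percentages as descriptive and say which GPs answer them.
- Reconcile the measurement times in Sections 3.2.1 and 3.2.2 with the April 2021 GP survey in Sections 4.2 and 4.3 and with the end of research in Section 7.8.1.

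The cost is one extra item in a questionnaire these GPs already receive. If the item cannot be added, the objective should be reworded as a description of competence after training.
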